### Sample size

Using a non-inferiority margin of 2.5%, with a power of 80% and 2.5% significance level and expecting the same response rate in each group, a minimum of 202 patients are required per randomised allocation group. Thus, a minimum total of 808 randomised eligible participants are necessary for statistical analysis. No adjustment will be made for carrying out three pair-wise tests. Secondary outcomes may not necessarily be powered.

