### Trial procedure

Potentially eligible participants who have been found eligible by a member of their own clinical care team acting as principal investigator (PI) at the research site, will firstly be randomly allocated to each of the four arms of the study. Following random allocation, potentially eligible participants will be asked to consent by the PI to the research study based on the method of administration they have been randomly allocated. The potentially eligible participants will receive an Invitation Letter, a Participant Information Sheet and a Consent Form via the post. The participant facing documentation will invite the participant to consent to the study and receive their 6-month review and the PRHSQs via one of the four methods they have previously been randomly allocated. Additionally, a proxy consent option is noted in the Participant Information Sheet and Consent Form, thereby allowing for a designee to offer consent on behalf of the participant via the principles of informed consent if the participant requires physical assistance to complete the questionnaire.

Following the initial contact, participants who have not responded will be contacted a second time; two working weeks following the dispatch of the first letter. The second contact will contain the same information as the initial contact (Invitation Letter, Participant Information Sheet and Consent Form). Potentially eligible participants will be given a further four working weeks to reply to the second invitation to participate. If no consent is returned, the potentially eligible participant will be assumed not to wish to take part and will not be asked to complete the PRHSQs.

For all potentially eligible participants who are randomised and invited to participate in the study, we will collect a range of background demographic data and a small number of routinely collected health-related data. See Table 1 for details of data for collection.

**Table 1 Tab1:** Demographic and routine clinical data for collection

Demographic data	Routinely collected clinical data
Date of birth DD/MM/YYYY	Classification of stroke: Cerebral Infarct (ICD I63) Cerebrovascular Haemorrhage (ICD I61) Stroke – not specified as Haemorrhage or Infarction (ICD I64)
Sex	Date of index event (date of stroke) Individual National Institutes of Health Stroke Score (NIHSS) on admission: 0–42
District-level postcode – First 3–4 digits of a UK post code	
	Treated with thrombolysis? Yes / No

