### Statistical analysis

#### Analysis of the primary outcome

We will carry out a difference of two proportions between the three intervention groups (postal, telephone or online) verses face-to-face administration, with a 2.5% non-inferiority margin. The three comparisons will be adjusted using a Holm [24] multiplicity adjustment, with a two-sided alpha = 0.05. The analysis will be presented as a difference with an associated 95% confidence interval (CI).

Analyst and researchers blinding to the allocation will remain in place until interpretation of the primary and secondary outcomes are agreed. Following un-blinding of the allocation, difference will be generated in the three comparator allocation groups, and face-to-face completion rate, and will include the non-inferiority margin of 2.5%, as our primary analysis.

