#### Secondary analysis of the primary outcome

We plan to repeat the primary analysis after adjustment for: age; sex; National Institutes of Health Stroke Score (NIHSS) on admission and stroke type (Haemorrhagic or Ischaemic).

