### Missing data and analysis population

We will be reporting using a complete case analysis. Due to the nature of the research question, we are expecting missing data, and anticipate that this will be not missing at random. We will describe patterns of missing data. However, the primary objective of this study is to ascertain if the missing data is systematically more likely in the comparator groups, compared to the face-to-face allocation group.

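### The deciding non-inferiority test is unadjusted although the plan already names and collects prognostic covariates; making the adjusted risk difference primary would be a low-cost, modest gain in precision

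*Protocol article*

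**What the plan says.** Under Analysis of the primary outcome, the protocol article states: "We will carry out a difference of two proportions between the three intervention groups (postal, telephone or online) verses face-to-face administration". Each difference is set against a 2.5-point margin, with a 95% CI and a Holm adjustment. No covariate is named for this test.

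Under Secondary analysis of the primary outcome it adds: "We plan to repeat the primary analysis after adjustment for: age; sex; National Institutes of Health Stroke Score (NIHSS) on admission and stroke type". It does not say how a difference in proportions will be adjusted.

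The covariates are meant to exist for non-responders too. Under Trial procedure: "For all potentially eligible participants who are randomised and invited to participate in the study, we will collect a range of background demographic data". The same sentence goes on to cover some routine health data, and Table 1 there lists "Individual National Institutes of Health Stroke Score (NIHSS) on admission: 0–42" along with date of birth, sex and stroke classification. The Data management section confirms that people who do not reply or consent stay in the analysis of these data.

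On gaps in the data, Missing data and analysis population says: "We will be reporting using a complete case analysis".

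**The concern.** Non-inferiority is decided by whether the lower confidence limit lies above -2.5 points, so the width of the interval matters directly. In a randomised trial, adjusting for baseline variables that predict the outcome narrows that interval. If the adjusted result is standardised back to a difference in proportions, the quantity estimated and the scale of the margin stay the same. The plan already holds the variables and names them, yet the analysis they would sharpen cannot carry the decision because it is labelled secondary.

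The document gives some reason to think these variables relate to return. The Secondary outcomes section plans return proportions by NIHSS and by stroke type, and the Discussion anticipates that demographic and clinical features will correlate with how many people consent under each method. Neither statement gives a strength.

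**Working it through.** **Inputs from the protocol article.** 202 per group, 80% power, 2.5% significance level and a 2.5-point margin (Sample size section: "Using a non-inferiority margin of 2.5%, with a power of 80% and 2.5% significance level and expecting the same response rate in each group"); 85% face-to-face return (Non-inferiority margin section; the Sample size section states no rate). The share of outcome variance explained by the covariates, R², is not given. I take 0.02 to 0.10 as the main range and show 0.20 as an optimistic case.

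**The plan's own figure.** n per group = 2p(1-p)(1.960 + 0.842)² / margin².
- At p = 0.85 and a 2.5-point margin: 0.255 × 7.849 / 0.000625 = 3203, not 202.
- At p = 0.85 and a 10-point margin: 0.255 × 7.849 / 0.01 = 201.
- With the 2.5-point margin kept, 202 would need a common rate of about 99.2%.

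This mismatch is a separate matter. It is shown because it limits what adjustment can achieve.

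**Effect of adjustment.** Unadjusted SE = √(2 × 0.85 × 0.15 / 202) = 3.55 points; half-width = 1.96 × 3.55 = 6.96 points. A standardised adjusted risk difference has variance of about (1 - R²) times the unadjusted variance. Power = Φ(2.5/SE - 1.96), with no true difference.

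| R² | Half-width (points) | Power at 2.5 points | Equivalent n per arm, 202/(1 - R²) |
|---|---|---|---|
| 0 | 6.96 | 10.5% | 202 |
| 0.02 | 6.89 | 10.6% | 206 |
| 0.05 | 6.79 | 10.8% | 213 |
| 0.10 | 6.61 | 11.2% | 224 |
| 0.20 | 6.23 | 12.0% | 253 |

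Reaching 80% power with 202 per arm would need R² = 1 - 202/3203 = 0.94.

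**Check with a fitted model.** Simulation used two arms of 202, 85% return in both, one prognostic covariate and two noise covariates, a logistic model standardised to a risk difference, and 4000 trials per scenario.

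| AUC | R² | Variance, adjusted / unadjusted |
|---|---|---|
| 0.50 | 0 | 1.01 |
| 0.61 | 0.02 | 0.98 |
| 0.69 | 0.06 | 0.94 |
| 0.75 | 0.12 | 0.91 |
| 0.83 | 0.22 | 0.81 |

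The formula is borne out approximately. At AUC 0.75 the fitted gain was 9%, somewhat below the 12% that the formula gives.

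**Lower return.** The Background cites stroke response rates of 36.4 to 70.1%, so 85% may be high for a questionnaire that follows a postal consent step. At 50% return the unadjusted SE is 4.98 and the half-width 9.75. R² of 0.02 to 0.10 brings the half-width to 9.65 to 9.25. The same AUC explains more variance at 50%: 7.7% at AUC 0.66 and 17.3% at AUC 0.74, treating the predictor as known. The half-width would then be about 9.4 to 8.9.

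**Missing covariates.** If a share m is dropped for missing baseline values, the variance scales as (1 - R²)/(1 - m). The gain is cancelled when m = R².

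**The case against.** The strongest reply is that nothing here is wrong. The unadjusted difference is valid under randomisation and estimates the stated primary outcome directly. It needs no covariate values, and an adjusted repeat is already pre-specified. That stands: a reader might infer that the primary analysis is faulty or that the covariates are thrown away, and the documents support neither.

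A reader might also infer that the plan forgoes free precision that could change the result. That does not stand either. The gain depends on a prognostic strength the documents do not give, and every half-width above remains far larger than 2.5 points.

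The Non-inferiority margin section may be read as expecting disability and communication problems to predict return. In fact it offers them as a possible reason why services choose face-to-face follow-up; it says nothing about who returns a questionnaire. The Secondary outcomes and Discussion sections are the proper support, and they are modest.

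Two technical objections can be answered. First, complete-case analysis could cancel the gain if NIHSS is often missing, but filling baseline gaps without reference to outcome keeps everyone in. Second, a logistic model on its own yields an odds ratio, which cannot be set against a margin in percentage points, but standardisation returns a risk difference.

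The randomisation stratum, centre, is in neither analysis. That is a separate question and does not alter this one.

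**Conclusion.** The point holds as an efficiency improvement, not as an error or a contradiction. The plan names useful covariates, intends to collect them on everyone, and leaves them out of the test that decides. If R² lies between 0.02 and 0.10, promoting the adjusted analysis is worth roughly 4 to 22 extra people per arm (202/0.98 and 202/0.90, less 202), and the expected cost if they predict nothing is about 1% in variance. The benefit rests on that assumed R² and on baseline gaps not removing people from the model. It is minor beside the sample-size mismatch, which adjustment cannot repair.

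**What to change.** Before unblinding, make the primary analysis a covariate-adjusted marginal risk difference for each mode against face-to-face:

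- Fit a logistic model with arm and all four covariates the plan already lists: age, sex, admission NIHSS and stroke type. Give unspecified stroke (ICD I64) its own level, because it is eligible but is not among the two types named for the adjustment.
- Standardise over all randomised people to a return proportion per arm. Compare the three differences, with robust 95% CIs, with -2.5 points under the plan's multiplicity rule.
- Fill missing baseline values by a rule that does not use outcome, such as the overall mean or a missing category, so that nobody is dropped.
- Report the unadjusted difference as the supporting analysis.

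The cost is analysis-plan wording and a little programming, with no new data. The downside is a headline figure slightly less simple to explain than two raw proportions.

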#### Secondary analysis of the primary outcome

We plan to repeat the primary analysis after adjustment for: age; sex; National Institutes of Health Stroke Score (NIHSS) on admission and stroke type (Haemorrhagic or Ischaemic).

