	Modified Rankin Score on discharge or transfer from stroke unit: 0–6
	Clinically confirmed diagnosis of aphasia as sequela of ICD I63, I61 or I64?: (data collected at 3 sites within a single Health Board only) Yes / No

All demographic data and routinely collected clinical data will be stored against a Participant Research Number in the research data base. Personally identifiable information will only be stored at the research sites and will not be stored for those who do not offer informed their consent before the cut-off period of 4 weeks following the posting of the second letter Therefore, no personally identifiable information will be held by the central research team.

All consented participants will receive the PRHSQs. The PI at site as a member of both the research team and the participant’s own care team will be responsible for arranging or delegating the completion of the questionnaires between 4 and 8 months post stroke. There are schema for each method by which the PI must abide; however, the methodologies for all four methods of administration differ slightly and are as follows:

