#### Secondary outcomes

The proportion of individuals eligible for the study who return the method specific PRHSQs in each of the four study arms (postal, online, face-to-face and telephone) for individuals with communication issues (i.e. aphasia)The proportion of individuals eligible for the study who return the method specific PRHSQs in each of the four study arms (postal, online, face-to-face and telephone) by stroke severity as defined by individual NIHSS on admissionThe proportion of individuals eligible for the study who return the method-specific PRHSQs in each of the four study arms (postal, online, face-to-face and telephone) by stroke type; Cerebral Infarct (ICD I63), Cerebrovascular Haemorrhage (ICD 161) or Stroke, not specified as haemorrhage or infarction (ICD I64)

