### Analysis of the secondary outcomes

Continuous data will be summarised descriptively, and also with a general linear model, and adjusted for patient age and sex. Dichotomous data will be summarised descriptively and will analysed using a logistic regression adjusted for: patient age and sex.

We note that many data will be gathered relating to the questionnaire itself. This useful clinical data warrants publication in its own right; however, it is not the focus of this study and will form a separate stand-alone analysis.

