### Non-inferiority margin

Utilising unpublished routinely collected clinical data approximately 85% of follow-up appointments for all patients, who would meet the inclusion criteria, return for face-to-face administration of their 6-month post-stroke follow-up assessment at the ≥ 4-month to ≤ 8-months post-diagnosis time point. The reason for this high level of face-to-face follow-up is not grounded on evidence, however, disability and communication issues post stroke may have a role in the choice of this method. Nevertheless, there is a significant cost implication in the choice of method for follow-up as evidenced in a study by Lannin et al. (2013) investigating the cost-effectiveness of telephone vs mail methods of follow-up for the Australian National Stroke Registry [10].

Alongside the National Institute for Health and Care Excellence (NICE) accredited RCP stroke guidelines [25], a non-inferiority margin of 2.5% was decided upon as the maximum tolerated acceptable reduction in acceptability, alongside conflicting resource allocation and offering flexibility of patients to undergo follow-up.

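### Disability at discharge (modified Rankin) is collected for everyone randomised and invited but enters no named analysis: a small loss of precision and an unreported breakdown, not a bias

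*Protocol article*

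**What the plan says.** The primary analysis is unadjusted: "We will carry out a difference of two proportions between the three intervention groups (postal, telephone or online) verses face-to-face administration" (Analysis of the primary outcome). A supportive repeat adds covariates: "We plan to repeat the primary analysis after adjustment for: age; sex; National Institutes of Health Stroke Score (NIHSS) on admission and stroke type" (Secondary analysis of the primary outcome). That list is closed. The Secondary outcomes section breaks return down by arm for people with aphasia, by stroke severity and by stroke type, and it fixes severity as the individual NIHSS on admission. The models for the secondary outcomes carry only two covariates: "Dichotomous data will be summarised descriptively and will analysed using a logistic regression adjusted for: patient age and sex" (Analysis of the secondary outcomes).

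Table 1 under Trial procedure also lists "Modified Rankin Score on discharge or transfer from stroke unit: 0–6". The text introducing the table says these data are gathered for every potentially eligible person who is randomised and invited. The questionnaire comes later: the site investigator is responsible for "arranging or delegating the completion of the questionnaires between 4 and 8 months post stroke".

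On why face-to-face follow-up is so common, the Non-inferiority margin section says that "disability and communication issues post stroke may have a role in the choice of this method".

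**The concern.** The margin section raises disability and communication together. Communication gets its own secondary outcome (aphasia). Disability gets none, although a disability score is in the dataset. The severity breakdown instead uses a neurological score from admission, before acute care and about 4 to 8 months before the questionnaire.

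A patient with a high admission NIHSS who recovers well, and one with a low score who leaves hospital dependent, are then grouped by something other than their ability to travel, write, use a computer or manage a telephone interview. Services would want to know which mode suits disabled survivors, and no named analysis tells them. Randomisation does not answer this part, because the value of a subgroup description depends on the variable that defines the groups.

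In the adjusted analysis the stake is precision: a prognostic baseline variable that is already collected is left out.

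**Working it through.** **Is there bias?** Three statements in the protocol settle this.
- Randomisation: permuted blocks of varying size, stratified within centre.
- Trial procedure: allocation comes first and consent is sought afterwards.
- Primary outcome: the denominator is all individuals eligible for the study, not only those who consent.

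Disability is therefore balanced between arms in expectation. Any chance imbalance is part of the sampling error that the confidence interval already covers.

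**How much precision is forgone?** The plan states no figure for this, so there is none to reproduce.

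Inputs from the protocol: 202 per arm (Sample size); about 85% return (Non-inferiority margin); margin 2.5 points. Assumed, not in the protocol: 40% dependent at discharge, with return 20 points lower (alternative: 10 points lower).

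1. SE of a difference at 85% in both arms: sqrt(2 × 0.85 × 0.15 / 202) = 0.0355, or 3.55 points.
2. SD of the chance imbalance in dependency between two arms: sqrt(2 × 0.4 × 0.6 / 202) = 0.0487, or 4.87 points.
3. Its contribution to the difference in return: 4.87 × 0.20 = 0.97 points. With a 10-point effect: 0.49 points.
4. Share of the variance: (0.0487 × 0.20 / 0.0355)² = 7.5%. With a 10-point effect: 1.9%.
5. SE if all of that is removed: a factor of sqrt(1 − 0.075) = 0.96, about 4% smaller. With a 10-point effect: sqrt(1 − 0.019) = 0.99, about 1% smaller.
6. Half-width of the 95% interval: 1.96 × 3.55 = 6.96 points, falling to 6.96 × 0.96 = about 6.7 points under the larger effect.

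Cross-check of step 4: return of 93% in independent and 73% in dependent patients averages 0.6 × 0.93 + 0.4 × 0.73 = 0.85. The between-group variance is 0.4 × 0.6 × 0.20² = 0.0096, and 0.0096 / (0.85 × 0.15) = 7.5%.

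**Illustrative simulation.** Two arms of 202, true difference zero, a six-level disability score with equal frequencies, return falling from 96% to 61% across the levels (average 82.5%), 20,000 runs.

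| | Unadjusted | Adjusted for disability |
|---|---|---|
| Mean estimated difference | −0.0001 | −0.0001 |
| SD of the estimate | 0.0380 | 0.0361 |

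The unadjusted 95% interval covers the truth in 94.8% of runs. The SD ratio is 0.0361 / 0.0380 = 0.95, so adjustment gains about 5% in the SE. Omitting the variable costs precision only.

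Both calculations compare adjustment for disability with no adjustment. The planned model already contains age and admission NIHSS, so whatever these explain of discharge disability must be subtracted. About 4% to 5% is thus an upper figure under these assumptions.

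**The case against.** The case against is strong on the main inference. The primary analysis is unadjusted and valid without Rankin, the adjusted repeat is supportive, and admission NIHSS is a legitimate prespecified baseline covariate. The severity outcome does what it says and does not claim to describe residual disability. All of that stands.

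Several stronger readings are tempting, and the protocol does not support them.
- **Residual disability is uncontrolled and distorts the comparison.** Pre-consent randomisation with all eligible individuals in the denominator rules this out.
- **A one-SD imbalance uses up 39% of the margin (0.97 / 2.5).** The arithmetic is right, but this is ordinary sampling error already inside the interval. Set against the margin, it looks like a distortion.
- **Rankin is used nowhere.** It is in no named analysis. However, Data management keeps non-consenters' routine clinical data for analysis, the missing-data section promises to describe patterns, and the Discussion expects to relate clinical features to consent by method. None of these lists variables, and an analysis plan that is not shown may do so. Equally, none of them specifies return by Rankin.
- **Rankin is better because it is closer in time.** The difference is only the length of the stroke-unit stay, which the protocol does not give. The real advantage is that Rankin measures disability after acute care.
- **The protocol names disability as the driver.** It says only that disability may play a part, and that the high level of face-to-face follow-up is not grounded on evidence.
- **Time since stroke should be adjusted for too.** Eligibility confines it to 4 to 8 months and randomisation balances it. The protocol gives no reason to adjust for it.

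What survives is narrower than these readings but is not a matter left open by the article. The covariate list and the definition of severity are fixed in the text, and they leave out the collected disability measure.

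**Conclusion.** The point holds as a modest improvement to the plan, not as an error in the primary result. The plan's own remark about disability is not matched by its named analyses, although the variable is in Table 1.

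In the supportive adjusted analysis the cost is at most about 4% to 5% of the SE under assumed strong prognostic effects, about 1% under the weaker assumption, and less once age and NIHSS are accounted for. The 40%, 20-point and 10-point inputs and the simulated return curve are assumptions. An interval half-width of about 6.7 instead of 7.0 points does not alter what the trial can conclude against a 2.5-point margin. Whether 202 per arm suits that margin is a separate question.

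The more useful loss is descriptive: return by arm according to disability is not among the named outputs.

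**What to change.** In Secondary analysis of the primary outcome, add modified Rankin score at discharge or transfer to the adjustment set, alongside age, sex, admission NIHSS and stroke type. In Secondary outcomes, also report return by arm by discharge modified Rankin, descriptively and in addition to the NIHSS breakdown. Fix both before unblinding. Leave the unadjusted primary analysis as it is, and do not add time since stroke.

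The cost is wording only, since Table 1 already provides for the variable. There are two small downsides. It adds one more unpowered breakdown, in a protocol that already warns that secondary outcomes may not be powered. Under the complete-case rule, patients with a missing Rankin score would also drop out of the adjusted model, so the number lost should be reported next to the adjusted estimate.
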